### Patient Withdrawal

Patients will be withdrawn from the study if, due to the occurrence of adverse events, it becomes difficult to continue the research; if patients or their parents or guardians request to end their participation; if the research study is discontinued; or if the principal investigator and subinvestigators judge it appropriate to discontinue the research.

### Study Procedures

Figure 2 illustrates the study enrollment procedure. After obtaining informed consent, pediatric patients will be randomly assigned to either a VR app group, which will undergo amblyopia treatment using the VR app for pediatric patients with amblyopia combined with full refractive correction glasses, or a control group, which will undergo amblyopia treatment based on occlusion treatment with an eye patch combined with full refractive correction glasses [24]. Patients assigned to the VR app group will use the VR app for amblyopia at home for 1 hour per day for 6 months, in combination with full refractive correction glasses. Patients assigned to the control group will follow occlusion therapy with an eye patch for 6 months, also wearing full refractive correction glasses, and the duration of eye patch use will be determined by the prescribing physician. Both groups underwent ophthalmological examinations on the first day of the trial and at weeks 4, 8, 12, 16, 20, and 24. Ophthalmological examinations will include measurements of visual acuity, intraocular pressure, strabismus angle, stereopsis, refractive error, and corneal curvature. Only the VR app group will perform a digital stereopsis test using the VR app once per week and complete a usability questionnaire on the VR app at weeks 2, 12, and 24. The week 2 visit conducted only for the VR app group is intended to confirm that the study participants, particularly those unfamiliar with VR devices, are using the VR app correctly and facilitate their continued appropriate use. Only the control group will record their daily duration of eye patch use in a diary. Study participation will end for both groups after the 24-week visit.

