### Inclusion and Exclusion Criteria

Outpatients who visit the collaborating study institutions will be recruited and must meet the following inclusion criteria: between 3 and 10 years old at time of enrollment; diagnosis of anisometropic amblyopia, strabismic amblyopia, or refractive amblyopia; best-corrected visual acuity (BCVA) of 0.3 logMAR or worse in the amblyopic eye at screening; and have a BCVA in the fellow eye of 0.2 logMAR or better at screening [19]. The inclusion age range was chosen because amblyopia treatment responsiveness declines with age, and improvement is less likely in older children. In this study, limiting enrollment to younger children was considered ethical because the VR-based intervention’s effectiveness remains uncertain.

In this study, amblyopia is confirmed before enrollment, and since anisometropic and refractive amblyopia may occur even with small interocular acuity differences, we did not require a 2-line difference as eligibility criterion, though commonly referenced as a diagnostic indicator of amblyopia [23]. The exclusion criteria will be as follows: inability to obtain consent from the legal guardian; where applicable, inability to obtain assent from the patient; history of intraocular surgery or refractive surgery; history of photosensitive epilepsy; inability to comply with the study protocol due to psychological, familial, or geographic reasons; or inability to perform hand-eye coordination tasks, as determined by physical or mental conditions or by observation during a trial use of the study device, indicating a clear inability to establish hand-eye coordination.

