**Patient characteristics**
Age, sex, medical history (including anisometropic amblyopia, strabismic amblyopia, and refractive amblyopia), and duration of treatment for amblyopia

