## Discussion

Pediatric amblyopia can cause an irreversible reduction in visual acuity and has a profound impact on the quality of life. The conventional therapeutic approach, comprising full refractive correction and occlusion of the healthy eye, has established efficacy. However, the substantial psychological and physical burden imposed on affected children predisposes them to poor adherence and compromises treatment effectiveness, thereby undermining the overall outcomes of amblyopia therapy. Therefore, therapeutic modalities that minimize the burden on pediatric patients and concurrently enhance patient adherence and therapeutic efficacy in the treatment of amblyopia are warranted. This protocol paper outlines a multicenter clinical trial designed to evaluate the therapeutic efficacy of a VR app for pediatric amblyopia. The implementation of VR app–based amblyopia training has the potential to improve treatment outcomes by enhancing adherence through gamification and augmenting therapeutic efficacy via hand-eye coordination.

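### Children may enter at any stage of glasses or patching treatment, and the primary comparison does not account for that stage, which costs precision and some ability to detect a VR deficit

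*Protocol article*

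**What the plan says.** The Inclusion and Exclusion Criteria section opens with "Outpatients who visit the collaborating study institutions will be recruited and must meet the following inclusion criteria". It then lists age, amblyopia type, "best-corrected visual acuity (BCVA) of 0.3 logMAR or worse in the amblyopic eye at screening", and the requirement to "have a BCVA in the fellow eye of 0.2 logMAR or better at screening". The only exclusions that concern earlier treatment or medical history are "history of intraocular surgery or refractive surgery; history of photosensitive epilepsy". Nothing refers to time in glasses, repeated or stable acuity, or previous or current patching.

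Study Procedures goes straight from consent to allocation: "After obtaining informed consent, pediatric patients will be randomly assigned to either a VR app group". No run-in or refractive adaptation phase is stated. Full-correction glasses are part of the assigned treatment in both arms; for the VR arm the wording is "VR app for pediatric patients with amblyopia combined with full refractive correction glasses".

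The article regards glasses as active treatment. The Introduction describes amblyopia treatment as corrective glasses together with patching, and the Discussion says: "The conventional therapeutic approach, comprising full refractive correction and occlusion of the healthy eye, has established efficacy".

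Textbox 1 lists "duration of treatment for amblyopia" among the patient characteristics. Sample Size and Statistical Analyses bases the primary conclusion on 95% confidence intervals for the 0-12 week BCVA change in each arm, with no covariate. The only adjusted models it names concern the associations with VR gameplay. The limitations in the Discussion mention severity, etiology, comorbidities, age and VR experience, but not treatment stage.

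**The concern.** Under these criteria, a child given first full-correction glasses at enrolment and a child long established in glasses and patching are equally eligible. The first may improve over 12 weeks because of the glasses, whichever arm is assigned. That gain is part of the primary endpoint.

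Two consequences follow for the between-arm comparison. First, treatment stage becomes a source of variation in the change score, and with 12 to 15 children per arm randomization may leave it unevenly split. Second, the primary question is noninferiority. Children whose acuity recovers through glasses alone show little or no difference between VR and patching, so they pull the average difference toward zero. In a superiority trial that works against the sponsor. Here it makes a real deficit harder to see.

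**Working it through.** **Inputs from the protocol article (Sample Size and Statistical Analyses).** SD 0.14 logMAR; margin 0.10; assumed difference 0.07, direction not stated and taken here as favouring VR; significance level 2.5%, taken as one-sided; power 90%; 12 evaluable per arm, 15 after 20% dropout.

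**Inputs that are assumptions.** The article gives none of these. A share f = 0.5 of children is new to full correction; 0.5 is the value that maximises the variance, and 0.3 is shown beside it. These children gain an extra g = 0.10 to 0.20 logMAR by week 12. For the dilution example, 30% resolve on glasses alone.

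1. *The plan's own sample size.* n per arm = 2 × 0.14² × (1.960 + 1.282)² / (0.10 + 0.07)² = 0.0392 × 10.51 / 0.0289 = 14.3, so 15 per arm. The stated 12 does not reproduce at one-sided 2.5%; it does at one-sided 5% (0.0392 × 8.56 / 0.0289 = 11.6, so 12). The dropout step does reproduce (24 / 0.8 = 30). This mismatch is a separate matter, and the present point does not rest on it.

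2. *Effect of treatment stage on the SD.* If 0.14 applies to children stable in glasses, SD = √(0.14² + f(1−f)g²).
   - f = 0.5, g = 0.10: √(0.0196 + 0.0025) = 0.149
   - f = 0.5, g = 0.20: √(0.0196 + 0.0100) = 0.172
   - f = 0.3, g = 0.10 and 0.20: √0.0217 = 0.147 and √0.0280 = 0.167

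   If 0.14 already reflects mixed treatment stages, nothing is added.

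3. *What that SD costs.* With f = 0.5 and the formula in step 1, n per arm rises from 15 to 17 (SD 0.149) or 22 (SD 0.172). Power with 12 per arm, Φ(0.17 / (SD × √(2/12)) − 1.96), falls from 84% to 80% or 68%.

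4. *Chance imbalance is the same effect.* At 15 per arm, the SD of the difference in the proportion of new wearers is √(2 × 0.5 × 0.5 / 15) = 0.183. Multiplied by g, this moves the between-arm difference by 0.018 to 0.037 logMAR per SD of imbalance, in either direction. It must not be added to step 2, because 2 × 0.14²/15 + 0.5g²/15 equals 2 × (0.14² + 0.25g²)/15. Both sides give a standard error of 0.054 for g = 0.10 and 0.063 for g = 0.20.

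5. *Dilution.* If the VR deficit is absent in the 30% who resolve on glasses, a true deficit of 0.12 averages 0.12 × 0.7 = 0.084. For a correct one-sided 2.5% test against 0.10, P(declare noninferiority) = Φ((0.10 − deficit)/(0.14 × √(2/n)) − 1.96).
   - n = 12, standard error 0.0572: deficit 0.12 gives Φ(−2.31) = 1.0%; deficit 0.084 gives Φ(−1.68) = about 4.7%
   - n = 15, standard error 0.0511: 0.9% and about 5.0%
   - For a deficit exactly at the margin with n = 12: 2.5% undiluted, about 8% if 30% resolve on glasses (average 0.07), about 14% if 50% do (average 0.05)

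6. *What adjustment recovers.* If the recorded stage captures the glasses gain fully, the residual SD returns to 0.14. The variance removed is 0.0025/0.0221 = 11% for g = 0.10 and 0.0100/0.0296 = 34% for g = 0.20, less one or two degrees of freedom. Adjustment does not undo the dilution in step 5; that needs a separate look at children established in full correction.

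**The case against.** The strongest reply is that the comparison is fair as it stands. Both arms wear full correction and allocation is random 1:1, so a shared glasses gain enters both arms equally in expectation. A reader might infer that the glasses effect confounds VR versus patching. The article does not support that: the mixing is in each arm's own change, not in the expected difference. This objection stands in full.

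A reader might also infer that already-patched children at a plateau handicap the control arm. That is not supported either. Study Procedures leaves patching duration to the prescribing physician, so the regimen may change at entry, and nothing indicates how many children are at a plateau or how they would respond to VR.

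The sponsor can fairly say that VR plus glasses against patching plus glasses in ordinary outpatients is the contrast intended, since the Primary Outcome section aims at efficacy under usual treatment conditions. It can add that extra variance widens the interval and makes noninferiority harder to show, that every effect size above is assumed, and that the cited source of the 0.14 may already include mixed stages. These points limit the size but do not remove the issue.

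Finally, covariates and stratification factors are often left to a full protocol or analysis plan. That would excuse silence. Here, however, the article states a primary criterion, and that criterion takes no covariate. The entry criteria are likewise given in detail, with reasons, and are not an analysis matter.

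**Conclusion.** The point holds as a matter of precision and sensitivity, not of bias. Children at any treatment stage are eligible, and the stated primary comparison leaves out a prognostic factor that the trial largely collects already.

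The size is moderate and conditional. The SD reaches 0.149-0.172 if half the children are new to full correction, gain an extra 0.10 to 0.20 logMAR, and 0.14 describes children stable in glasses; otherwise the rise may be nil. The two components pull in opposite directions: added variance makes noninferiority harder to declare, while dilution makes it easier. An average deficit of 0.084 lies inside the margin, and a reader might take that to mean a 0.12 deficit would usually pass. It would not: the chance goes from about 1% to about 5% with a correct test.

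This is an improvement the sponsor should make. It does not make the trial uninterpretable.

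**What to change.** Record two items at baseline: the date full correction began, and prior patching (yes/no). The treatment duration already collected does not by itself separate time in glasses from time patching. Then estimate the week-12 between-arm difference in BCVA change with adjustment for new versus established full correction and for prior treatment, using that duration. Add a sensitivity analysis restricted to children established in full correction. If half qualify, that is about 15 of the 30 children, so it should be read for direction and consistency, not as a test.

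The cost is two case report form fields and one or two model terms in a small trial. No child's entry is delayed.

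Requiring stable acuity in full correction before entry would address the source of the problem, but it is an option for the sponsor to weigh and not a required change. It delays entry in an age group in which the Introduction says responsiveness declines after about 7 years, and it slows recruitment within an enrolment window from January to September 2026 at three sites.

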**Figure 2. F2:**
[figure not shown]
Study flowchart. VR: virtual reality.

### Data Collection and Outcome Assessments

The data collection items are listed in Textbox 1. Data on patient characteristics, ophthalmological examination results, VR app malfunctions, and adverse events will be collected from both the VR app and control groups. The daily usage time of the VR app, stereopsis test results obtained via the VR app, and usability evaluation results were collected only for the VR app group. Daily eye patch usage time will be collected only in the control group.

Visual acuity will be measured by BCVA using the Landolt-C chart at a distance [25]. Intraocular pressure will be measured using a noncontact tonometer [26]. The strabismus angle will be assessed using the alternate prism cover test [27]. Stereopsis will be evaluated using the Titmus stereo test [28]. The refractive error and corneal curvature radius will be measured using an autorefractor keratometer [29]. Daily VR app usage time will be calculated from the VR app usage logs, and daily eye patch wearing time will be reported by the patient’s parent in a diary.

Textbox 1.Data collection.

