**Methods:**

This is a multicenter, open-label, prospective, randomized controlled trial that will be conducted at 3 centers in Tokyo, Japan. Pediatric patients aged 3-10 years with anisometropic, strabismic, or refractive amblyopia will be enrolled. Participants will be assigned 1:1 to a VR app group or a control group. The VR app group will use the VR app at home for 1 hour per day for 6 months. The control group will undergo conventional occlusion therapy with an eye patch for 6 months. Each group will comprise 15 participants (30 participants in total). Ophthalmologic examinations will be performed at baseline and at weeks 4, 8, 12, 16, 20, and 24. The primary endpoint will be the change in the best-corrected visual acuity in the amblyopic eye from baseline to week 12. Secondary endpoints will include changes in best-corrected visual acuity, stereopsis, and ocular deviation through week 24. We will also assess treatment adherence, defined as the ratio of the cumulative actual treatment time to the cumulative prescribed time; record adverse events, and evaluate usability in the VR app group. Longitudinal changes in outcome measures will be analyzed using a mixed-effects model.

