### Adherence Evaluation

Treatment adherence will be evaluated for VR app usage and eye patch wearing, defined as the ratio of the actual treatment time to the target treatment time. In the VR app group, the target daily treatment time will be 1 hour of VR app usage per day, and the ratio will be calculated by dividing the actual VR app usage time by the total target treatment time (number of participation days in the study multiplied by 1 h). In the control group, the sum of the daily eye patch wearing times prescribed by the physician will constitute the target treatment time. This ratio will be calculated by dividing the actual eye patch wearing time by the total target treatment time throughout the study period.

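### Adherence is tested between arms on an app log in one arm and an open-label parent diary in the other, so a difference, or the lack of one, cannot be attributed to behaviour

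*Protocol article*

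**What the plan says.** All references are to the protocol article.

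- **Numerator.** Data Collection and Outcome Assessments states: "Daily VR app usage time will be calculated from the VR app usage logs, and daily eye patch wearing time will be reported by" the parent, by diary. Study Procedures confirms that the diary exists in one arm only: "Only the control group will record their daily duration of eye patch use in a diary".
- **Denominator.** The Abstract gives one verbal definition for both arms, "defined as the ratio of the cumulative actual treatment time to the cumulative prescribed time". Adherence Evaluation applies it arm by arm. The VR target is "number of participation days in the study multiplied by 1 h". For controls, "the sum of the daily eye patch wearing times prescribed by the physician will constitute the target treatment time", and the ratio is obtained by "dividing the actual eye patch wearing time by the total target treatment time throughout the study period".
- **Comparison.** Secondary Outcomes (item 4) compares the ratio between arms at weeks 4, 8, 12, 16, 20 and 24. Sample Size and Statistical Analyses assigns two-tailed t tests or repeated-measures mixed-effects models at a two-sided 5% level.
- **Status.** Secondary Outcomes lists adherence among the key secondary endpoints and says that all secondary outcomes are read as exploratory.
- **Intended conclusion.** The Conclusions paragraph of the Abstract says the study will clarify whether the app improves adherence as well as treatment outcomes.

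**The concern.** No child has both measures. Every VR value comes from a machine log, and every control value comes from a parent who knows the assignment. Any systematic error in the diary therefore enters the between-arm difference in full, and none of the planned models contains information that could remove it. This cannot be left to the analysis stage, because the missing measurement has to be collected during the trial.

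Higher adherence is one of the main reasons given for developing the app, and the Abstract promises a conclusion on it. The Discussion lists five limitations, including the unvalidated VR stereopsis test, but the difference in adherence measurement is not among them.

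**Working it through.** The plan gives no expected adherence, standard deviation or power for this endpoint, so there is no figure to reproduce. The check sets the two definitions side by side and then illustrates the size.

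**Side by side**

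| | VR app arm | Control arm |
|---|---|---|
| Actual time | app usage log | parent diary |
| Target time | 1 h per participation day | sum of physician-prescribed times |
| Span as worded | participation days | study period |

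The first row is the decisive difference. The second row is each arm's own prescription, which is a legitimate way to normalise. The third row is a difference of wording that should be aligned.

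**Size of the artefact**

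Inputs: true adherence of 0.50 in both arms, borrowed from the Introduction, which cites a study finding that patients wore the patch for about half the prescribed time; relative diary over-reporting r of 10% to 40% (assumption).

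Observed control ratio = 0.50 × (1 + r):
- r = 10%: 0.50 × 1.10 = 0.55, a gap of 5 points against a logged VR ratio of 0.50.
- r = 40%: 0.50 × 1.40 = 0.70, a gap of 20 points.

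**Masking a real benefit**

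Suppose true adherence is 0.70 with the app (assumption) and 0.50 with the patch. With r = 20% the observed difference is 0.70 − 0.60 = 0.10, half the true 0.20. With r = 40% it is 0.70 − 0.70 = 0.

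**Effect on a test**

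Take one two-sided 5% two-sample t test, equal true adherence, and a between-child standard deviation of 0.20 to 0.30 (assumption). The noncentrality is shift / (SD × √(2/n)). For n = 15 and SD 0.25, the denominator is 0.25 × √(2/15) = 0.0913, so a 10-point shift gives 1.10 and a 20-point shift gives 2.19, on 28 degrees of freedom.

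| Diary shift | 15 per arm, SD 0.25 | 15 per arm, SD 0.20-0.30 | 12 per arm, SD 0.20-0.30 |
|---|---|---|---|
| none | 5% | 5% | 5% |
| 10 points | 18.5% | 14-26% | 12-22% |
| 20 points | 56% | 42-75% | 35-65% |

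Entries are the chance of a significant difference when behaviour is the same in both arms. At 50% true adherence, 10 and 20 points correspond to r = 20% and r = 40%. The plan's multiplicity adjustment over repeated visits would lower these rates, but it would leave the bias in the estimate unchanged.

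**The case against.** The strongest reply is that the endpoint is exploratory, that the Abstract's Objective is visual acuity, and that future confirmatory trials are called for. All of this stands and limits the weight of the point. It does not answer it: an exploratory label tempers the claim but does not remove a systematic error, and the Abstract still intends a conclusion on adherence.

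Three stronger readings are tempting, and the documents do not support them.

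- **That the denominators are also confounded with arm.** The Abstract gives one definition, actual over prescribed time, and each arm is divided by its own prescription. A reader might note that a VR child who plays fully for 28 days and leaves scores 100% on participation days but 28/168 = 17% over 24 weeks. That contrasts two rules within one arm; it shows no difference between arms. The article does not say that the control denominator runs on after withdrawal. Nor does "the duration of eye patch use will be determined by the prescribing physician" say that the prescription changes during the trial, and a sum of prescribed times would absorb a change.
- **That the bias could favour either arm.** The two mechanisms one would name, over-reporting in the diary and the diary acting as a reminder, both raise the control ratio and so work against the app. If over-reporting were established, a result in favour of the app would be conservative. The documents do not give the direction of diary error.
- **That the trial's objective depends on adherence.** Adherence is rationale and expected benefit; no primary or confirmatory claim rests on it.

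It is also fair to say that a diary in the VR arm is a weaker instrument than the log, and that parents who know use is logged may report differently from patching parents. The diary should therefore be added to the log and should not replace it.

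**Conclusion.** The concern holds for the numerator. As planned, a between-arm difference in adherence, or its absence, mixes behaviour with method of measurement, and no analysis of the data as collected can separate them. Under the assumed 10-40% relative over-reporting at 50% true adherence, the control ratio is inflated by about 5 to 20 points. That is enough to hide a benefit of the app or to suggest an advantage of patching. The over-reporting range and the standard deviations are assumptions; the confounding itself follows from the text alone. The different wording of the two time spans is a minor point of alignment. The change should be made, but its reach is limited to an exploratory key secondary endpoint, and the primary visual acuity comparison is untouched.

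**What to change.** 1. Have VR-arm parents complete the same daily diary as control parents. Report a diary-against-diary comparison alongside the log-based VR ratio.
2. Within the VR arm, compare diary with log to gauge over-reporting, and state that the estimate may not transfer exactly to patching.
3. In Adherence Evaluation, use the same span for both denominators, for example from randomisation to the visit or to withdrawal.
4. If the diary is not added, report the two ratios descriptively by arm without a between-arm test. List the measurement difference as a limitation that qualifies the adherence statement in the Abstract's Conclusions.

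The cost is a diary and a small daily reporting burden for about 15 families, plus a sentence in the adherence definition. The diary must be kept prospectively, so it should be introduced as early as possible. The fallback in item 4 needs only wording.
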